**Fig 1 pone.0355953.g001:**
[figure not shown]
Disposition of participants.

At follow up visits, after reviewing the medical history records and measuring height, weight, and blood pressure, distance visual acuity with or without glasses and pinhole will be measured using the LogMAR chart for both eyes of each participant.

The Basic Protocol involves community-level imaging platforms, including CFP, OCT, and OCTA, which would be performed on both eyes of each participant (without pupil dilation) using Topcon 3D OCT-1 (Maestro 2) according to the settings mentioned in Table 1.

For participants who are part of the Enhanced Protocol, the imaging modalities will include Ultra Widefield Fundus Photography, OCT, FAF, and OCTA, and will all be performed according to the setting described in Table 2.

**Table 2 pone.0355953.t002:** Detailed enhanced imaging protocol.

Imaging modality	Imaging protocols (through dilated pupils)
Optical Coherence Tomography (OCT)	Heidelberg Spectralis (Heidelberg engineering, Heidelberg, Germany) Spectral-Domain OCT, wavelength of 870 nm, A-scan speed of 70,000 scans per second, axial resolution: 3.9 µm, transverse tissue resolution: 6 µm Perform cube scan 6x6mm scan, centred on the fovea (macula), 97 horizontal B-scan, 512 A-scans per line, Automatic Real Time (ART) 7–9, and Enhanced Depth Imaging (EDI) mode on.
Optical Coherence Tomography Angiography (OCTA)	Zeiss PlexElite (PlexElite 9000, Carl Zeiss Meditec) Swept-Source OCTA, wavelength of 1050nm, A-scan speed of 100,000 scans per second Perform en-face OCTA scans with 3x3mm and 6x6mm scan, centred on the fovea (macula) DREAM OCT (Vg200, Intalight) Swept-Source OCTA, wavelength of 1070nm, A-scan and speed of 400,000 A-scans per second Perform 29 x 24 mm OCTA scan (1536 x 1280, R2), centred on the fovea (macula)
Fundus Autofluorescence (FAF)	Heidelberg Spectralis OCT Excitation blue light of 488 nm and a barrier filter beginning at 500 nm Capture two images at 30 and 50 degrees (ART > 50), centred on the fovea (macula), with the optic disc clearly visible in the image Optos (Nikon, Tokyo, Japan) Ultrawide Field FAF
Ultrawide Field Fundus Photography	Optos (Nikon, Tokyo, Japan) Capture one shot at 200 degrees of the retina, centred on the fovea (macula) and includes optic disc

OCT scans will be repeated in the case of motion artifacts and/or low signal strength (SS) (Spectralis OCT Q < 30, Zeiss OCTA SS < 7). Automated retinal segmentation and slab boundaries in OCT and OCTA scans will be manually checked and corrected in case of segmentation errors.

Blood collection is optional and will only be performed for willing participants. Thirty milliliters of venous blood sample will be collected in EDTA tubes at any point during the 5-year follow-up period. The freshly collected blood has to be processed in the laboratory within 6 hours of collection. Upon Ficoll centrifugation of the blood specimen, a buffy coat layer containing mononuclear cells and neutrophils at the bottom of the tube will be isolated. These samples would be stored at –80°C for up to 15 years for genetic and metabolomic analysis at SERI.

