**Methods:**

This prospective, longitudinal cohort study aims to recruit 1500 participants from community-based cohorts in Singapore, with a follow-up duration of 5 years. Eligible participants are adults aged 55 years or older without severe systemic illness that would preclude participation.

At baseline, demographic data and medical history will be collected, and visual acuity will be assessed. A basic imaging protocol including color fundus photography (CFP), optical coherence tomography (OCT), and OCT angiography (OCTA) will be performed. Blood samples will be collected from consenting participants. Images will be graded for early signs of AMD, defined as the presence of pathological findings on CFP, OCT, or OCTA.

Participants without early signs of AMD will undergo annual follow-up using the basic imaging protocol. Those with any pathological findings at baseline or during follow-up will undergo an enhanced imaging protocol every 6 months, including ultrawide-field fundus photography, fundus autofluorescence (FAF), OCT, and OCTA. All follow-up visits will be conducted at the Singapore Eye Research Institute (SERI).

Multimodal imaging biomarkers will be integrated with clinical, demographic, genetic, and metabolomic data to assess the relative risk of progression and identify potential predictors. The study protocol has been approved by the SingHealth Centralised Institutional Review Board.

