## Methods

### Study setting

This is a prospective, longitudinal cohort study designed to recruit participants from community cohorts in Singapore. Community cohorts were selected specifically to ensure the study cohort was generalizable to an overall population. Following the recruitment and baseline visit, over a five-year period, participants will undergo follow-up ophthalmic assessments at the Singapore Eye Research Institute (SERI).

Our specific aim is to establish the natural history of AMD in Asian elderly and to identify clinical multimodal imaging, genetic, and metabolomic predictors of progression. Progression is defined as the change from early signs of AMD to advanced AMD. Our secondary aims include: 1- define thresholds for referable early AMD suitable for community screening, 2-formulate an Asian-specific image classification system against existing AMD frameworks.

This will ultimately lead to developing personalized monitoring strategies for at-risk individuals and also inform a comprehensive and standardized community screening approach for the early detection and monitoring of AMD.

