	Complete RPE and outer retinal atrophy (cRORA)	(1) a region of hypertransmission of at least 250 µm in diameter, (2) a zone of attenuation or disruption of the RPE of at least 250 µm in diameter, (3) evidence of overlying photoreceptor degeneration, and (4) absence of scrolled RPE or other signs of an RPE tear
OCTA		• Choroidal vascularity index (CVI) • Choriocapillaris flow area Those variables will be measured by the DREAM OCT in-built software and the average values at Early treatment diabetic retinopathy study (ETDRS) 0–1, 0–3, 0–6 mm areas will be documented. Abnormal flow signal in the outer retina/sub-RPE space or neovascular network visible on en-face view of those slabs

* These variables will be graded just in late AMD stage

The primary study outcome will be progression to late AMD, defined as 1- neovascular AMD (the development of macular neovascularization (MNV)) and/or 2- Geographic atrophy (GA, defined as atrophy lesions seen on CFP and FAF and further confirmed by the presence of complete retinal pigment epithelium and outer retinal atrophy (cRORA) on OCT, in the absence of present or previous MNV), during follow-up.

The rate of progression to late AMD will be reported, with event time assigned to the first visit at which GA or MNV is detected. The rate and time to event of progression from non-exudative neovascular AMD, detectable abnormal flow signal in the outer retina/sub-RPE space on OCTA and no exudative sign or macular fluid on OCT imaging, to exudative neovascular AMD will also be reported.

The prevalence of each multimodal imaging biomarkers alongside the rate of quantitative biomarkers and their longitudinal changes will be reported. By integrating those biomarkers with clinical (medical, drug and social history), genetic, and metabolomic data, we will assess their relative risk for progression and will present potential predictors. Furthermore, the identified prognostic factors may be used to explore clinically meaningful risk strata and inform the development of an AMD staging framework tailored to the Asian population. Using that classification, the rate of progression to different stages of AMD through years of follow-up will be reported.

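### Blood for metabolomic predictors may be drawn at any time in the 5 years, so some progressors can be sampled only after late AMD is detected

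*Protocol article*

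**What the plan says.** The blood paragraph, under Data collection, examinations, and imaging (after Table 2), sets the collection rule: "Blood collection is optional and will only be performed for willing participants", and then "Thirty milliliters of venous blood sample will be collected in EDTA tubes at any point during the 5-year follow-up period". The same stored material serves both laboratory purposes: "These samples would be stored at –80°C for up to 15 years for genetic and metabolomic analysis at SERI".

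Study setting makes it part of the specific aim "to identify clinical multimodal imaging, genetic, and metabolomic predictors of progression". Grading of retinal imaging and outcomes to be measured commits to the estimate: "By integrating those biomarkers with clinical (medical, drug and social history), genetic, and metabolomic data, we will assess their relative risk for progression". That section also dates the outcome, "with event time assigned to the first visit at which GA or MNV is detected".

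The abstract says only "Blood samples will be collected from consenting participants". The sentence sits in the paragraph on the baseline visit and carries no time of its own.

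**The concern.** A predictor has to be measured before the outcome it predicts. The collection rule does not secure that order. A participant may progress in year 2, stay in follow-up and give blood for the first time in year 4. The metabolite level then reflects late AMD, any treatment for it and two more years of age. Entered as a predictor, it can show an association that runs from disease to marker.

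Two features make the loose window more than a formality:

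- **The loss is permanent.** An analysis plan can discard post-event samples, but it cannot supply the pre-event sample that was never drawn. Only the collection window prevents this.
- **Opportunity to be sampled depends on disease status.** Participants with early signs attend every 6 months and the others once a year. Those at higher risk therefore have about twice as many occasions to give blood, and draw timing may follow disease status.

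At stake is the metabolomic part of the stated aim. Progression rates and imaging predictors do not use the blood sample, and germline genotype does not change when the eye progresses.

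**Working it through.** The document gives no power, event or effect figure for blood markers, so there is nothing to reproduce. The calculation below illustrates the size under stated assumptions.

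**Inputs from the document.** The draw is allowed anywhere from 0 to 5 years. The event is dated at the first visit with GA or MNV. Follow-up continues to 5 years, and no rule orders the draw and the event.

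**Assumptions.** Progression time T is uniform on 0 to 5 years. Draw time D is independent of T. Progressors stay in follow-up until they are sampled.

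**Share of sampled progressors drawn after the event.** With T uniform on 0 to 5, P(D > T) = mean(D) / 5.

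| Assumed draw timing | Mean draw time (years) | Share drawn post-event |
|---|---|---|
| All at baseline | 0 | 0% |
| Uniform over year 1 | 0.5 | 0.5/5 = 10% |
| Uniform over years 0 to 2 | 1.0 | 1.0/5 = 20% |
| Half at baseline, half uniform over 0 to 5 | 1.25 | 1.25/5 = 25% |
| Uniform over years 0 to 5 | 2.5 | 2.5/5 = 50% |
| All in year 4 to 5 | 4.5 | 4.5/5 = 90% |

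Replacing the uniform event time by a constant hazard hardly matters. For uniform draws over 0 to 5 years the share is 50.0% to 50.9% as the 5-year risk goes from 0.51% to 10%.

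**What such a share could do to an estimate.** Take a metabolite with no effect on progression that shifts by s SD once late AMD is present. If a share q of progressors is sampled after the event, their mean is raised by q × s, and the spurious odds ratio per SD is about exp(q × s).

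| Shift s | q = 10% | q = 25% | q = 50% |
|---|---|---|---|
| 0.5 SD | 1.05 | 1.13 | 1.28 |
| 1 SD | 1.11 | 1.28 | 1.65 |

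The shifts are assumed. The approximation ignores the small extra variance from mixing pre-event and post-event samples.

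**Immortal time, as a separate case.** If post-event samples are dropped but time is still counted from enrolment, a participant sampled at year d must be event-free until d. The event rate in such participants is then (5 − d)/5 of the true rate: 0.90 for d = 0.5, 0.80 for d = 1 and 0.50 for d = 2.5. If time at risk starts at the draw, this dilution is zero.

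**The case against.** Several objections have force.

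- **Analysis rules may be elsewhere.** Time origin, delayed entry and the handling of post-event samples belong in an analysis plan that is not shown. This stands for immortal time. A reader might infer that immortal-time bias is built into the study, but the article fixes no time origin for metabolomic models. The bias arises only if the marker is treated as a baseline covariate with time counted from enrolment. The objection does not reach the collection rule, which the article states and no analysis plan can undo.
- **The two biases do not add up.** A reader might combine the 50% post-event share with a mean 2.5 years of immortal time. They belong to different analyses. If post-event samples are kept, the time before the draw is not event-free; if they are dropped, the contamination disappears. The dilution in the last calculation also concerns absolute event rates. A hazard ratio for a metabolite would be distorted by that route mainly if its level varied with draw time.
- **The event count is unknown.** A reader might apply the cited 0.51% to 1,500, get 7.65 progressors, and conclude that a few misdated samples decide the result. The Sample size section gives that rate for adults aged 40 or over and expects a higher one here; an assumed 2% would give 30. Blood is optional, so the metabolomic denominator is also below 1,500 if anyone declines. Too few events would be a problem whenever blood is drawn, and Strengths and limitations already acknowledges it.
- **The abstract is not a flat contradiction.** Its blood sentence has no date. The fit with the Methods is loose and needs only an editorial change.
- **Metabolomic variables are not listed as candidates in Statistical methods.** That list is permissive, and the aim and the outcomes section both commit to metabolomic predictors.

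**Conclusion.** The point holds for the metabolomic part of the aim and should be fixed. As written, a metabolomic predictor may be measured after the outcome it is meant to predict, and pre-event samples may be lost for good.

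The share of sampled progressors affected runs from 0% if everyone is drawn at baseline, through 10% (year 1) and 20% (years 0 to 2), to 50% if draws are uniform over the 5 years. These figures rest on evenly spread progression and on draw timing independent of it. The document gives no draw-time distribution, so none of them is a forecast.

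The documents do not support a wider conclusion. Progression rates, imaging predictors and germline genetics do not carry this reverse causation, and immortal time remains conditional on an analysis choice that is not shown.

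**What to change.** 1. In the blood paragraph, replace the open window for metabolomic blood: draw at baseline, or at the first SERI visit where the 6-hour processing limit prevents a draw in the community.
2. Record the draw date for every sample.
3. In metabolomic progression models, use only samples drawn before late AMD is detected in **either** eye. Blood is a person-level measure while the analysis is by eye, so a rule confined to the eye analysed would still admit blood taken after late AMD in the fellow eye. A draw at the visit of first detection does not count as before.
4. Start time at risk in those models at the draw.
5. Use later samples for genetics only.
6. Align the abstract with the revised wording.

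The first-SERI-visit option reduces the problem without removing it. That visit falls at about 6 or 12 months, by which time 0.5/5 = 10% or 1/5 = 20% of progressors would have had their event under even spread. Step 3 turns these into excluded samples, so they no longer contaminate the estimate.

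The cost is somewhat fewer metabolomic samples and cases, including participants who already have late AMD in one eye when first sampled. No procedure is added. According to Timeline of the study, 64 of the 1,500 participants (64/1,500 = 4.3%) had been recruited at submission, so nearly all draws can still follow the new window.

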## Introduction

Age-related macular degeneration (AMD) is a leading cause of vision impairment globally, particularly among individuals aged 50 and older, posing a significant challenge to public health [1,2]. AMD primarily affects the macula, leading to progressive central vision loss that severely impacts daily activities such as reading, driving, and recognizing faces, thereby diminishing patients’ overall quality of life [3,4]. With the global population aging rapidly, particularly in regions like Europe, North America, and Asia, the prevalence of AMD is projected to rise sharply [1]. This trend has profound implications for public health systems, demanding enhanced healthcare resources and interventions to manage the growing burden of vision impairment.

Despite its global impact, the incidence, clinical presentation, progression, and subtypes of AMD show significant variation across different populations [5,6]. Large-scale epidemiological studies, such as the Singapore Epidemiology of Eye Diseases (SEED) study and Beijing Eye Study, have shed light on these population-specific differences, highlighting unique AMD phenotypes and risk factors among Asians [6–9]. For instance, polypoidal choroidal vasculopathy (PCV), a distinct subtype of AMD, is notably more prevalent in Asian populations compared to Western populations, where traditional AMD hallmarks, such as drusen or soft drusen, are more commonly observed [9,10]. These distinctive features underscore the necessity for Asian-specific research to better understand the underlying mechanisms, risk factors, and clinical manifestations of AMD in this population.

While there is consensus regarding features that predispose to late AMD, at an individual level, risk, rate, and pattern of progression remain unpredictable; therefore, there is a need to develop effective AMD screening. This contrasts with diabetic retinopathy because the natural history is well understood, and the risk of vision loss increases sharply in those with referable DR. In AMD, this threshold is not yet established.

This paper describes the methodology of our study, designed to track retinal aging changes and understand the natural progression of AMD in a multi-ethnic Asian population. We hypothesize that there are specific high-risk features identifiable through multimodal imaging and systemic biomarkers that are associated with progression of AMD.

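### The only blood fraction named for storage is a leukocyte layer; followed as written, no plasma is banked for the metabolomic predictors in the specific aim

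*Protocol article*

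**What the plan says.** The blood procedure is in the protocol article, Methods, in the last paragraph before the section on grading of retinal imaging. Giving blood is optional. For those who agree, "Thirty milliliters of venous blood sample will be collected in EDTA tubes at any point during the 5-year follow-up period". On timing, "The freshly collected blood has to be processed in the laboratory within 6 hours of collection". After Ficoll centrifugation, "a buffy coat layer containing mononuclear cells and neutrophils at the bottom of the tube will be isolated". The paragraph closes: "These samples would be stored at –80°C for up to 15 years for genetic and metabolomic analysis at SERI".

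The use of these samples is set elsewhere. Under Study setting, the specific aim is to "identify clinical multimodal imaging, genetic, and metabolomic predictors of progression"; this is the main aim, listed ahead of the two secondary aims. The Introduction hypothesises "specific high-risk features identifiable through multimodal imaging and systemic biomarkers that are associated with progression of AMD". The Abstract and the section on grading and outcomes both plan to combine metabolomic data with imaging, clinical and genetic data when assessing the relative risk of progression.

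**The concern.** The isolated fraction consists of white cells. That is a sound source of DNA and serves the genetic part of the aim. It is not the fraction in which small molecules circulating in the blood are found; those are in the plasma, which is separated from the cells at this step. A reader who takes the hypothesis about systemic biomarkers together with the metabolomic part of the aim would expect plasma or serum to be stored, and the procedure names neither.

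A cellular measurement is also sensitive to handling. Cells left in whole blood continue to metabolise. The article allows up to 6 hours before processing, gives no holding temperature, and then puts the cells through a gradient. Differences in delay between participants would add variation unrelated to AMD. DNA tolerates this well; metabolites tolerate it much less.

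At stake is whether the bank can support one of the predictor classes in the specific aim. Plasma not kept when a tube is processed cannot be recovered later from the frozen cells.

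**Working it through.** The article gives no figure to reproduce. The check is a comparison of what is stored with what the aim needs, followed by one small calculation.

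**1. What is stored.** The isolation sentence can be read as one layer holding both cell types, or as a mononuclear layer plus neutrophils lying at the bottom of the tube. Either way the material is leukocytes. The next sentence refers back to these samples, and the nearest thing it can refer to is the isolated cell material.

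**2. Whether another fraction is stored.** The Abstract, Introduction, Study setting, blood paragraph, grading and outcomes, Statistical methods, Safety measurements, Data management, and Strengths and limitations were read for any mention of blood, samples, genetics or metabolomics. None mentions plasma or serum, whether as kept or as discarded.

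**3. What the stored samples are for.** The same sentence assigns them "for up to 15 years for genetic and metabolomic analysis at SERI". So the article does more than leave the metabolomic specimen open: it gives the named cell fraction both uses.

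**4. What the aim needs.** Study setting asks for metabolomic predictors without naming a matrix. The Introduction speaks of "specific high-risk features identifiable through multimodal imaging and systemic biomarkers", again with no matrix. No assay platform is given.

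**5. Putting these together.**

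| Use | Specimen named in the article | Adequate as written? |
|---|---|---|
| Genetic | Leukocyte fraction | Yes |
| Cellular metabolites | Leukocyte fraction, up to 6 h before processing | Possible in principle; exposed to delay |
| Plasma or serum metabolites | None | No |

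**6. How much plasma is already in the tube.** The draw is 30 mL (blood paragraph). The plasma fraction of whole blood is not in the article; assume 0.40 to 0.57.

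- Lower end: 30 mL × 0.40 = 12 mL
- Upper end: 30 mL × 0.57 = 17.1 mL

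On that assumption about 12 to 17 mL of plasma per donor is present before separation, so no further blood would be needed to bank aliquots.

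**7. How much of the cohort is still ahead.** Timeline of the study reports 64 recruited; Sample size gives a target of 1,500. 64 / 1,500 = 4.3%, so about 95.7% of planned recruitment remained at manuscript submission. The article does not say how many of the 64 gave blood.

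**The case against.** The strongest reply is that this is a journal article giving blood handling one short paragraph. Aliquoting, the fractions kept and the matrix for each assay usually sit in a laboratory manual, which is not shown. The article says that a layer is isolated; it does not say that only this layer is kept. The isolation sentence is also loosely worded and may be a summary rather than a bench procedure. This much stands: a reader might infer that the plan excludes or discards plasma, and the text does not state that. It does not dispose of the point, because the article does not defer to a manual. It names a fraction and gives that fraction to metabolomics. If plasma is banked, the paragraph misdescribes the metabolomic specimen and needs correcting anyway.

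Three other inferences are tempting and are not supported:

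- That metabolomic work is impossible. Leukocyte metabolites can in principle be assayed, and the article assigns the samples to that use.
- That the aim promises circulating metabolites. That word is not used; the article says metabolomic predictors and systemic biomarkers.
- That there is already a permanent loss. The article neither limits donors to one draw nor reports that any of the 64 recruits has given blood. Collection is allowed throughout follow-up, so a donor could in principle be asked again, subject to approval and consent.

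It is also fair to say that metabolomic variables are not among the candidate covariates listed in Statistical methods, and that blood is optional. Both limit how far the problem reaches.

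**Conclusion.** The point holds in conditional form. The article names a Ficoll-isolated leukocyte fraction as the only stored specimen for both genetic and metabolomic analysis. Carried out as written, this leaves no plasma for any blood donor, so plasma metabolites could not serve as predictors under the specific aim or as systemic biomarkers under the hypothesis. Cellular metabolites would remain, after a delay of up to 6 hours.

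The reach is one predictor class, among those who consent to give blood. Progression to late AMD as graded on imaging, the discrete-time analysis, the imaging predictors and the genetic analyses are unaffected.

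The conclusion assumes that the paragraph describes the whole procedure. If a manual already provides for plasma, what is left is a correction to the text. The matter is worth settling before further samples are processed, because the remedy is cheap and plasma lost at processing cannot be regained from that draw.

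**What to change.** Amend the blood paragraph so that plasma is separated from the same EDTA tubes before the cell layer is isolated, aliquoted, and frozen at -80°C. Name plasma as the metabolomic matrix and keep the leukocyte fraction for genetics. Log draw and freeze times for every sample: the delay of up to 6 hours applies to plasma too, and a recorded time allows it to be adjusted for.

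The cost is a changed laboratory instruction and a few cryovials and freezer positions per donor. No extra blood, visit or participant procedure is needed.

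Two alternatives would also resolve the point:

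- If plasma is already banked under a laboratory manual, correct the paragraph to say so.
- If leukocytes are the intended matrix, state and justify this, and limit the metabolomic wording in the Abstract, Study setting, and the grading and outcomes section to cellular metabolites.
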